**Sample**					
**Character**	Separate hard lumps	Sausage-shaped but lumpy	Like sausage or snake, smooth and soft	Fluffy, ragged edges, mushy stool	Waterly, no solid pieces
**Score**	1	2	3	4	5

#### Safety assessment and dispose

The type, time of occurrence, severity, and duration of the adverse events will be recorded in detail from days 0 to 28. If emesis, severe diarrhea, dehydration, skin injury, fainting, infection, or other severe adverse events occur, the participants should be discontinued immediately from treatment and given appropriate treatment directly at the located hospital. And then, the detailed adverse event will be reported to the Ethics Committee.

### Adherence improvement

Parents will be offered free health counseling during the study. After the dropout or at the end of the full treatment, parents will be asked to hand over the remaining probiotics. Post the study, if the children still have constipation symptoms, they will be given three free pediatric *Tuina* sessions or two courses of probiotics.

### Sample size

A previous relevant study showed the effective rate of pediatric *Tuina* was 92.5% and Medilac-Vita was 72.5% [35]. Based on our own clinical experience, we consulted pediatric *Tuina* and physician experts. We anticipate an effective rate of 90% in the pediatric *Tuina* group and 70% in the Medilac-Vita group. Considering *α* = 0.05, 1-*β* = 0.90, *p*_1_ = 0.90, *p*_2_ = 0.70, *u*_0.05/2_ = 1.96, *u*_0.1_ = 1.282 [36], $$n=1641.4\times {\left[\frac{\left(1.96+1.282\right)}{\sin \sqrt[-1]{0.90}-\sin \sqrt[-1]{0.70}}\right]}^2$$ = 79.02 ≈ 79. With a drop-out of 10%, 88 FC children will be finally recruited in each group. Totally, 176 participants will be finally recruited in this study.

### Data collection

In this study, an independent data administrator will collect data every 3 months, from three assessors. The data of each participant includes basic information and outcomes. The basic information includes the participant’s gender, age, height, weight, history of pregnancy and delivery, past medical history, present condition, phone, and WeChat number of parents or legal guardians. Outcomes will be collected four times from baseline to the end of follow-up.

### Data monitoring

After the collection, the independent data administrator will check the CRFs to ensure data integrity and continuity. If in doubt, the stool diary and CRFs will be checked.

### Data management

The CRFs completed in 5 hospitals will be sent to the research office based in the School of Second Clinical Medicine, Yunnan University of Chinese Medicine. Two team members who are blind to the group allocations will perform double-data entry and summarize the data into an electronic dataset. Meanwhile, the data administrator will monitor and check for errors again. The data administrator and statistician will be blind to the group allocations and have the right to access the final dataset.

### Statistical analysis

The statistician will perform statistical analysis by using SPSS 19.0 statistics software (IBM Co., Armonk, NY, USA) and GraphPad 7.04 statistics software (GraphPad Software Co., San Diego, California, USA). Continuous variables are presented as the mean and standard deviation (SD). While the nonnormally distributed variables are presented as the median and interquartile range (IQR). Categorical variables are described as numbers and percentages (%).

Before the comparison, the normality and homogeneity of variance will be tested. Normality of continuous variables (SBMs, CSBMs, m-BSFS, distress sensation, and glycerine enema rate) will be determined by *Shapiro-Wilk* test, *Kolmogorov-Smirnov* test, *Skewness*, and *Kurtosis*. Homogeneity of variance of continuous variables will be determined by *F* test, *Brown-Forsythe*, and *Bartlett’s* test. Independent-Sample *t*-test or nonparametric test (*Mann-Whitney* test) will be used when compared between two groups. Paired *t*-test or nonparametric test (*Wilcoxon* test) will be performed to compare within a group. For the categorical variables (effective rate), the *χ*^2^ test will be performed to evaluate the significance of the difference. The statistical analysis will be a 2-sided test with a significance level of 0.05.

The missing data were will be dealt with expectation maximization, last observation carried forward method or listwise deletion. Subgroup analysis will be conducted according to the subject’s age (< 4 years and ≥ 4 years), which depends on the normality and homogeneity of variance of the data.

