## Methods/design

### Study design

This study is a prospective, randomized, multicentre, controlled design, and it will be conducted from December 2021 to December 2024. We will recruit 176 participants from 5 hospitals in 3 different provinces (Yunnan province, Zhejiang province, and Shandong Province). The eligible participants will be randomly allocated to 2 groups in a 1:1 ratio. The randomization sequence will be computer generated by the Clinical Research Center of the Yunnan University of Chinese Medicine. Every participant will receive a 1-week treatment period and a 2-week follow-up. Basic information and outcomes will be assessed at baseline and after each week. The flowchart is shown in Fig. 1, and the schedule is shown in Table 1.

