### Randomization and blinding

Eligible FC children will be randomly assigned into two groups at a 1:1 ratio, based on the random number. There are two different types of interventions in this study. It is impossible to blind therapists and children’s parents or legal guardians. Nonetheless, outcome assessors and the data analyst will be blinded to the procedure and results of randomization, group allocation, and intervention.

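### The test for weekly SBMs and CSBMs is chosen by normality and variance checks and uses no baseline value, age group or hospital: valid, but the effect measure is left open and precision is lost

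*Protocol article*

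**What the plan says.** All points are in the Protocol article.

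- **Choice of test (Statistical analysis).** "Before the comparison, the normality and homogeneity of variance will be tested". Four normality checks are named (Shapiro-Wilk, Kolmogorov-Smirnov, skewness, kurtosis) and three variance checks (F, Brown-Forsythe, Bartlett). A t-test or a Mann-Whitney test then compares the groups. The section does not say what happens if the checks disagree.
- **Error level.** "The statistical analysis will be a 2-sided test with a significance level of 0.05".
- **Within-group tests.** A paired t-test or Wilcoxon test "will be performed to compare within a group".
- **Age subgroup.** An analysis at under 4 and 4 years or older is planned, "which depends on the normality and homogeneity of variance of the data".
- **What is recorded.** Under Study design: "Basic information and outcomes will be assessed at baseline and after each week". Table 1 starts the stool diary at day −7. Data collection lists age, and Participants names five hospitals. Age group also sets the amount of treatment in both arms (Interventions).
- **Randomisation.** "Eligible FC children will be randomly assigned into two groups at a 1:1 ratio, based on the random number". No stratification factor is stated.

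**The concern.** Three features of the text combine.

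1. **The estimand follows the data.** A t-test addresses a difference in means; Mann-Whitney compares ranks. With seven checks and no rule to reconcile them, the primary effect measure is settled only after the data are seen. For small weekly counts the checks also carry little information, because normality will nearly always be rejected.
2. **Prognostic information is unused.** None of the named between-group tests takes a covariate. A child's baseline SBM count is likely to predict later counts, and leaving it out wastes information already collected. This matters more because the sample size was derived from the effective rate, a secondary outcome. The protocol states no power for SBMs or CSBMs.
3. **The age analysis is tied to the same checks.** As worded, the subgroup sentence lets distributional tests govern an analysis that should be reported whatever the shape of the data.

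At stake are power for the primary outcomes and a clear, pre-stated effect measure. The validity of the randomised comparison is not at stake.

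**Working it through.** **Step 1. Reproduce the plan's sample size.** Inputs from Sample size: "We anticipate an effective rate of 90% in the pediatric *Tuina* group and 70% in the Medilac-Vita group"; two-sided α 0.05; power 0.90.

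- asin√0.90 = 71.57°, asin√0.70 = 56.79°, difference 14.78°.
- n = 1641.4 × (3.242 / 14.78)² = 79.02, so 79 per arm.
- 79 / 0.90 = 87.8, so 88 per arm and 176 in total, as stated: "With a drop-out of 10%, 88 FC children will be finally recruited in each group".

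The figure reproduces. It concerns the effective rate only, so 79 per arm is used below simply as the evaluable number.

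**Step 2. What baseline adjustment is worth, by formula.** With correlation ρ between baseline and follow-up, ANCOVA has residual variance (1 − ρ²) times the unadjusted variance. Suppose the unadjusted comparison has 80% power at 79 per arm. The standardised difference is then (1.960 + 0.842) × √(2/79) = 0.446, and adjusted power is Φ(2.802/√(1 − ρ²) − 1.960). The protocol gives no ρ, so a range is shown.

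| Assumed ρ | Variance removed | Power with ANCOVA | n per arm for 80% |
|---|---|---|---|
| 0 | 0% | 80.0% | 79 |
| 0.2 | 4% | 81.6% | 76 |
| 0.3 | 9% | 83.6% | 72 |
| 0.5 | 25% | 89.9% | 60 |
| 0.7 | 49% | 97.5% | 41 |

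**Step 3. The planned rule on count data.** Assumed model: Poisson counts with a shared gamma frailty; baseline mean 2, control 4, treated 5; 79 per arm; 4,000 runs per setting. The rule was Shapiro-Wilk in each arm, then a t-test if both passed and Mann-Whitney otherwise, on follow-up values.

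| Frailty shape | Correlation | Normality accepted | Planned rule | ANCOVA | Gain (points) |
|---|---|---|---|---|---|
| 12 | 0.19 | 0.3% | 68.9% | 73.4% | 4.5 |
| 6 | 0.32 | 0.0% | 57.4% | 66.2% | 8.8 |
| 3 | 0.48 | 0.0% | 43.5% | 56.6% | 13.1 |

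With no treatment effect, the planned rule rejected in 4.8% to 5.3% of runs.

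**Step 4. Other assumptions, and change scores.** With assumed means of 3.2 and 4.2, 79 per arm and correlations from 0.10 to 0.56, ANCOVA exceeded Mann-Whitney on follow-up values by about 2 to 22 points and Mann-Whitney on changes by about 5 to 13. Repeating this gave the same pattern, with the ends of the ranges moving by two or three points according to the setting. The two ranges run in opposite directions. Ignoring baseline costs most when the correlation is high. Subtracting it costs most when the correlation is low: with equal variances a change score has 2/(1 + ρ) times the ANCOVA variance, or 1.54 at ρ = 0.3 and 1.18 at ρ = 0.7.

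**Step 5. Age and hospital.** The protocol contains nothing from which their contribution to precision could be calculated.

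**The case against.** The strongest reply is that nothing here is invalid. An unadjusted comparison in a 1:1 randomised trial is unbiased, and chance imbalance adds variance, not bias. That stands. A reader might infer that choosing the test from the data inflates false positives, but the simulated error rates do not show it.

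Several other tempting readings also go too far:

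- **Raw follow-up values are compared.** The protocol does not say so; changes are equally possible. In one assumed setting (frailty shape 2) a t-test on changes had 65% power against 63% for ANCOVA; at shape 4 it was 68% against 72%. If changes were compared by t-test, much of the loss could disappear. A change score is also more symmetric than a count, so near-certain selection of Mann-Whitney applies to the counts themselves.
- **The loss is large.** That needs a high correlation. Having two or fewer defecations per week is one of the entry criteria, though not a required one, and may narrow the baseline range. Limiting simulated baselines to two or fewer lowered the correlation to 0.30 and 0.20, with gains of about 12 points (39% to 51%) and 5 points (58% to 63%). With 1,200 runs, each percentage carries a Monte Carlo error of up to about 1.4 points, √(0.25/1200).
- **Age is ignored.** It is not: a subgroup analysis by age is planned. It is only absent as a covariate.
- **The subgroup analysis may be skipped.** The sentence can also mean that only the test used within each age group depends on data shape. The wording is ambiguous, and that is the defect.
- **Within-group tests are meant as proof of efficacy.** The protocol does not say this, and its stated hypothesis is comparative.

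It can also be argued that covariates and interaction tests belong in an analysis plan that is not shown. That would excuse silence. Here the article names the between-group tests and the selection procedure, and the point is addressed to that text.

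**Conclusion.** The point holds as one of efficiency and prespecification. The stated procedure leaves the effect measure for the primary outcomes to a set of checks with no tie-break. For weekly counts it will nearly always end in an unadjusted Mann-Whitney test. Type I error is unharmed.

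The size is conditional. At 79 per arm and assumed correlations of 0.1 to 0.56, a baseline-adjusted model gains about 2 to 22 power points over Mann-Whitney on follow-up values and about 5 to 13 over Mann-Whitney on changes. These figures rest on assumed means and a gamma-Poisson model, because the protocol supplies no SBM mean, SD or correlation. The direction against Mann-Whitney was the same in every setting tried, but at low correlation the gain over follow-up values is small. No figure can be put on adjustment for age and hospital. The subgroup and within-group points are matters of wording. The change should be made, since it is free, but the trial does not fail without it.

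**What to change.** 1. Stop using normality and variance tests to select the between-group analysis. They may remain as description.
2. Prespecify one model for weekly SBMs: ANCOVA with robust standard errors on group, baseline SBMs, age group (under 4, 4 or older) and hospital. Report the adjusted mean difference with its confidence interval, and give a negative-binomial model as sensitivity analysis.
3. Use the same model for CSBMs, with baseline CSBMs, in the children in whom they are assessed.
4. Reword the subgroup sentence so that the age analysis of SBMs is always reported, through a group-by-age interaction with the effect in each age group, independently of any distributional test.
5. State that within-group paired tests are descriptive and do not measure the treatment effect.

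The cost is a revision of the Statistical analysis text before unblinding. Every variable needed is already collected, and sample size, visits and data collection are unchanged.

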#### Secondary outcomes

The secondary outcomes are effective rate, stool form, distress sensation, and glycerine enema rate. The effective rate is the number of participants who are effective (on average, at least one bowel movement in 3 days, stool softening, defecate unobstructed) divided by a total number of the group. Stool form will be measured according to the modified Bristol stool form scale (m-BSFS) (Table 3), which classifies the form of children’s feces into 5 types from separate hard lumps (type 1) to entirely watery (type 5) [33, 34]. Distress sensation measured in the range of 0–3 represents the intensity of distress during defecation, “0” means no cry or grimace, “1” means slight cry and grimace, “2” means medium cry and grimace, and “3” means hysterical cry and grimace. Glycerine enema rate is the times of using glycerine enema divided by the times of defecation, within a week.

**Table 3 Tab3:** Modified Bristol stool form

**Type**	1	2	3	4	5

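### Stool form (m-BSFS) is tested as a continuous 1–5 score although smooth, soft stool sits at 3 and watery stool at 5, so a higher mean or rank is not necessarily better

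*Protocol article*

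**What the plan says.** Stool form is one of four secondary outcomes: "The secondary outcomes are effective rate, stool form, distress sensation, and glycerine enema rate" (Protocol article, Secondary outcomes). The modified Bristol scale "classifies the form of children’s feces into 5 types from separate hard lumps (type 1) to entirely watery (type 5". In Table 3 each type carries its own number as a score. The middle category, score 3, is described as "Like sausage or snake, smooth and soft", and the top category, score 5, as "Waterly, no solid pieces".

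The Statistical analysis section then fixes how the score is handled. It is named among the continuous outcomes: "Normality of continuous variables (SBMs, CSBMs, m-BSFS, distress sensation, and glycerine enema rate". The summary follows from that: "Continuous variables are presented as the mean and standard deviation (SD", with median and interquartile range if the data are not normal. Arms are compared by independent t-test or Mann-Whitney. The effective rate is the only outcome named as categorical.

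The article defines no target type, no normal range and no distance from type 3. Its safety section treats loose stool at its severe end as harm: "If emesis, severe diarrhea, dehydration, skin injury, fainting, infection, or other severe adverse events occur", treatment is stopped and the event is reported to the ethics committee.

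**The concern.** A comparison of means or ranks has a clear meaning when each step up the scale is a step in the same clinical direction. Here it is not. From 1 to 3 the score moves away from constipation. Towards 5 it moves into watery stool.

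Two things can follow. An arm with looser stools can show a higher mean that a reader takes for benefit. And an arm with more well-formed stools can look no different from one with a mixture of hard and watery stools.

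This matters because the Discussion names stool form, with defecation frequency, as a difference between Tuina and probiotics that the trial investigates, and it hopes the results will support guidelines.

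**Working it through.** **Inputs.** Scores 1 to 5 and their descriptions: Secondary outcomes and Table 3. Tests and two-sided 0.05 level: Statistical analysis. Number per arm: Sample size. The distributions over the five types are assumptions, since the article gives none.

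**The plan's own figure.** With angles in degrees, 1641.4 × [(1.96 + 1.282) / (arcsin√0.90 − arcsin√0.70)]² = 79.02, so 79 per arm before dropout, as stated. It rests on the effective rate and does not depend on stool form. It is used below only as the number per arm.

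**Arithmetic on the scale.**
- One child at type 1 and one at type 5 average (1 + 5)/2 = 3, the smooth and soft category.
- Moving from type 3 to type 5 adds 2 points, as does moving from type 1 to type 3.
- Moving a share *w* of children from type 3 to type 5 raises the arm mean by 2*w*: 0.10 for 5%, 0.30 for 15%, 0.60 for 30%.
- Mann-Whitney uses only the order of the scores and also places type 5 above type 3.

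**Illustrations where watery stools occur** (simulation, 79 per arm, one stool per child; percentages are types 1/2/3/4/5).

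1. 10/15/50/15/10 against 25/15/20/15/25.
   - First mean: 0.10 + 0.30 + 1.50 + 0.60 + 0.50 = 3.00. Second: 0.25 + 0.30 + 0.60 + 0.60 + 1.25 = 3.00.
   - Types 3–4: 65% against 35%.
   - Rejection: t-test 5%, Mann-Whitney 6%, types 3–4 as a proportion 97%.
2. 5/15/65/15/0 against 5/15/30/20/30.
   - Means: 0.05 + 0.30 + 1.95 + 0.60 + 0 = 2.90 against 0.05 + 0.30 + 0.90 + 0.80 + 1.50 = 3.55.
   - Rejection: t-test 99%, Mann-Whitney 97%, with the watery arm higher.
3. Less extreme: 10/25/50/10/5 against 25/20/25/15/15.
   - Means: 0.10 + 0.50 + 1.50 + 0.40 + 0.25 = 2.75 against 0.25 + 0.40 + 0.75 + 0.60 + 0.75 = 2.75.
   - Rejection: t-test 5%, Mann-Whitney 6%, type 3 as a proportion about 90%.

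**Illustrations where change is mostly at the hard end** (same set-up).

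4. 10/45/40/5/0 against 30/35/30/5/0 (means 2.40 and 2.10): t-test 64%, type 3 alone 27%, types 3–4 25%.
5. 10/25/45/18/2 against 25/30/35/8/2 (means 2.77 and 2.32): t-test 83%, type 3 alone 25%, types 3–4 71%.
6. 10/30/50/8/2 against 25/35/32/6/2 (means 2.62 and 2.25): t-test 73%, type 3 alone 64%, types 3–4 73%.

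Cases 1–3 show what the score can hide or blur. Cases 4–6 show that a proportion alone can lose much of the power to detect a shift away from hard stool.

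**The case against.** **No direction is claimed.** A reader might infer that the plan counts a higher m-BSFS as better and would declare the looser-stool arm the winner. The article does not say so. Table 3 describes type 5 plainly, so a mean well above 3 would be recognisable as loose stool. This stands. What remains is that, with no target type stated, a difference in means or ranks has no fixed interpretation.

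**Averaging within a child is not stated.** A reader might also infer that one child's hard and watery stools are averaged to a normal value. The article does not say how several stools in a week are combined. Offsetting is supported only across children, through the arm mean.

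**The illustrations are extreme.** All participants have functional constipation and treatment lasts one week. Nothing in the article suggests that 25–30% of stools would be watery. If nearly all stools lie in types 1–3, score and benefit move together. This stands and limits the size of the point. It does not remove the point, because the plan offers no safeguard if looser stools do occur.

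**Harm is recorded elsewhere.** Severe diarrhoea is captured as an adverse event with type, severity and duration, so severe harm is not hidden in the score. Milder loosening is less clearly covered, and the effective rate does not bound it: its stool-softening element has no upper limit.

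**An analysis plan may add detail.** A table by stool type could well be left to a document not shown. But the classification as continuous and the two tests are fixed in the article.

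**Conclusion.** The point holds in a limited form. The article explicitly classes m-BSFS as continuous, and its own scale puts smooth, soft stool in the middle and watery stool at the top. Neither planned test can tell movement towards type 3 from movement past it.

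The consequence is confined to one of four secondary outcomes. Its size depends on the share of watery stools, which the documents do not give: negligible if stools stay within types 1–3, large in the assumed cases with 15–30% watery stools in one arm. That type 5 is undesirable rests on its description and on the safety section's listing of severe diarrhoea, since no normal range is stated.

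It would go too far to conclude that the score should be dropped. In cases 4 and 5 it is more powerful than the proportion of type 3 stools (64% against 27%, and 83% against 25%). Adding a complementary analysis is a worthwhile, inexpensive improvement.

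**What to change.** Keep the m-BSFS comparison, described as measuring the shift away from hard stool, and state that values above the normal type are not counted as benefit.

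Alongside it, prespecify:
- the share of stools, or of children, in a normal range fixed before the data are seen (for example types 3–4, with type 3 alone as a sensitivity analysis), saying how a child's several stools in a week are combined;
- the shares of hard (types 1–2) and watery (type 5) stools, reported separately by arm.

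The article labels no type as normal, so the trial team must choose and justify the range.

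**Cost.** A change of wording and one more secondary analysis. The stool diary already records stool form, and the sample size is unaffected. The proportion can be markedly less powerful than the score when change is mostly from type 1 to type 2, so it should be added and should not replace the score.

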### Drop out criteria

The children’s parents voluntarily asked to withdraw.Patients have a sudden illness during the study.Patients receive other pharmacological or non-pharmacological interventions during the study period.Patients experience severe adverse reactions during the study.The stool diary records are largely missing and incomplete.

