### Interventions

To ensure all manipulations follow the standard procedures. The therapists in this trial own an official medical license and hold a master’s degree in pediatric *Tuina*. During this period, participants are not allowed to use any other interventions, at least in principle. If participants take any other interventions in this period, they will be defined as non-adherent and will be dealt with drop out.

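### Post-randomisation events are classed as drop-out and three unranked missing-data methods are allowed, so the plan as written permits a selective completers-only comparison

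*Protocol article*

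**What the plan says.** The Drop out criteria section of the protocol article lists five reasons: parental withdrawal, sudden illness, and the three quoted here.

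- "Patients receive other pharmacological or non-pharmacological interventions during the study period"
- "Patients experience severe adverse reactions during the study"
- "The stool diary records are largely missing and incomplete"

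The Interventions section repeats the first of these as a handling rule: "If participants take any other interventions in this period, they will be defined as non-adherent and will be dealt with drop out".

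Under Statistical analysis, the whole provision for missing data is: "The missing data were will be dealt with expectation maximization, last observation carried forward method or listwise deletion". It gives no order of preference and does not link a method to an outcome.

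Under Secondary outcomes, the effective rate is the number of effective children "divided by a total number of the group". The text does not say whether that total means the children randomised or those remaining.

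On blinding, the article says: "It is impossible to blind therapists and children’s parents or legal guardians". The Stool diary section gives the diary to the parents or guardians. Outcome assessors and the data analyst are to be blinded.

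**The concern.** All five drop-out reasons arise after randomisation, and at least two can be consequences of treatment. A severe reaction may be caused by it. A parent who knows the allocation and sees no improvement may look for other treatment, and the Discussion itself notes that most parents want quick relief. How fully a diary is kept may also depend on how the parent views the allocated treatment.

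If such children are deleted, the groups compared are no longer those that randomisation created. The resulting bias can go in either direction, and blinding the assessor or the analyst does not remove it, because the selection happens before the data reach them. The other two methods keep the child but have problems of their own, and the plan does not say which of the three will produce the reported result.

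There is also an irreversible element. A later analysis plan can define an analysis set, but it cannot recover diary weeks that were never collected because the child was treated as a drop-out.

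**Working it through.** **1. The plan's own figure.** Inputs from Sample size: 90% and 70% effective, two-sided alpha 0.05, power 0.90, drop-out 10%.

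- Angles in degrees: arcsin√0.90 = 71.565 and arcsin√0.70 = 56.789, difference 14.776.
- n = 1641.4 × (3.242 / 14.776)² = 79.02, so 79.
- 79 / 0.90 = 87.8, so 88 per group and 176 in total.

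The figure reproduces. Exact power of the uncorrected chi-square test is 90.2% with 79 per arm and 92.7% with 88. The inflation from 79 to 88 treats drop-outs as contributing nothing: the trial is powered on those who remain.

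**2. Listwise deletion with no true difference.** Let p be the true effective rate, d the share of an arm deleted and r the effective rate among those deleted. The completers' rate is (p − d·r) / (1 − d). Assume p = 0.70 in both arms, 88 randomised per arm, and r = 0 unless stated. The values of d and r are assumptions.

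| Deleted, Tuina / control | Completers' rates | Difference | Rejection rate |
|---|---|---|---|
| 10% / 10% | 0.70/0.90 = 77.8% in both | 0 | 5% |
| 15% / 5% | 0.70/0.85 = 82.4%; 0.70/0.95 = 73.7% | +8.7 points | about 25% |
| 10% / 10%, control loss random (r = 0.70) | 77.8%; 70.0% | +7.8 points | about 20% |

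The 25% is by exact enumeration (a normal approximation gives 26%); the 20% is a normal approximation. The second row loses 10% overall, which is what the plan expects. Reversing the imbalance reverses the sign.

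**3. Listwise deletion with the planned difference.** Suppose half of the not-effective children in each arm are deleted: 5% of the Tuina arm and 15% of the control arm.

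- Loss: 88 × 0.05 + 88 × 0.15 = 17.6, or 10% of 176.
- Rates: 0.90/0.95 = 94.7% and 0.70/0.85 = 82.4%.
- The difference falls from 20 to 12.4 points. Exact power with 83 and 74 children is 71.6%, against 90.2% when the same 10% is lost at random.

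So losing the same fraction of failures in both arms dilutes a true difference. If instead each arm loses 10% of its children, all not effective, the rates are 0.90/0.90 = 100% and 0.70/0.90 = 77.8%, and the difference rises to 22.2 points. Even balanced loss has no fixed direction when a true effect exists.

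**4. Last observation carried forward.** The schedule (Table 1) gives treatment on days 0 to 6 and assessments on days 0, 7, 14 and 21. A child lost before day 7 has only the baseline value, which would be carried through all three weeks. A child lost after day 7 has the value reflecting the treatment week carried into two weeks without treatment. The first assumes no change; the second assumes that the on-treatment response persists.

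**5. Expectation maximization.** This is valid if loss depends only on what has been recorded. It is doubtful where a child leaves because of a reaction or poor response in the week that is missing.

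**6. Counting drop-outs as not effective.** With 10% lost independently of outcome, the rates over 88 randomised are 0.90 × 0.90 = 81% and 0.90 × 0.70 = 63%. The difference is 18 points and exact power is about 77%.

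**The case against.** Several parts of the case for the plan stand.

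- Being classed as a drop-out is not the same as being removed from the analysis. The article nowhere says that data already collected are discarded, and two of the three methods retain the child. Only listwise deletion strictly conditions on completers.
- A reader might infer that children are removed because treatment failed or harmed them. The article does not say that. Failure is not a listed reason; linking other treatment to failure is a plausible inference. Parental withdrawal and sudden illness are also on the list.
- The calculations concern the effective rate, a secondary outcome (though the one that set the sample size). Its denominator may already include drop-outs, in which case the completers' rates above would not arise for it. No comparable figure can be given for weekly SBMs or CSBMs, because the article supplies no means, variances or loss patterns.
- The loss scenarios are assumed, and balanced selective loss gives no false positives.
- A reader might infer that the open choice among three methods in itself inflates type I error substantially. The documents offer no basis for a figure, and the blinding of the statistician limits a choice made by arm.
- An article may leave the definition of the analysis set to a fuller document, so its absence is not the point here.

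These limit the size and certainty of the concern. They do not answer it: the article itself fixes the drop-out rules and itself names deletion as one of three options of equal standing.

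**Conclusion.** The concern holds as a fault in what the article states. Events that can depend on arm and outcome are made drop-out criteria, in a trial where parents are unblinded and supply the outcome data, and the plan then permits deletion, carrying forward or expectation maximization without a rule. Following it as written can produce a biased completers-only comparison. It need not, since the plan equally allows methods that keep these children.

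Size is illustrative only. With no true difference and 70% effective in both arms, a 15% versus 5% loss of not-effective children gives a spurious 8.7 points and about 25% false positives against the nominal 5%. Equal loss of this kind gives none. With the planned 90% versus 70%, losing half the failures in both arms reduces the difference to 12.4 points. All of this assumes deletion and a denominator of those remaining. The arithmetic of the sample size is not in question.

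**What to change.** Before recruitment starts (Trial status places the trial in the training stage):

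1. State that every randomised child is analysed in the allocated group.
2. Separate stopping treatment from stopping data collection. Continue the diary to day 21 unless consent to data collection is withdrawn. Table 1 already runs the diary to that day.
3. Replace the three-method menu for weekly SBMs and CSBMs with one prespecified likelihood-based repeated-measures model over weeks 1 to 3, with baseline as covariate. It too assumes missing at random, so add a prespecified sensitivity analysis for data not missing at random.
4. Define the effective-rate denominator as all randomised children, with missing outcomes counted as not effective.
5. Keep the completers' analysis as a sensitivity analysis only.
6. Reconcile glycerine enema use, which Secondary outcomes treats as an outcome, with the rule in Drop out criteria and Interventions that any other intervention makes a child a drop-out. The article does not say how the two fit together.

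The cost is wording, continued follow-up of children who stop treatment, and a more conservative estimate. If 10% are lost independently of outcome and counted as not effective, power with 88 per arm is about 77% rather than the planned 90%. The protocol should state this. Continued diary collection reduces the cost by leaving fewer outcomes missing.
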